**Fig 3 pone.0309816.g003:**
[figure not shown]
Overview of the study design for the experiment on diagnostic performance. FOV: field-of-view, KK: Kato-Katz. Figure created using BioRender.com.

In absence of a gold standard, it will be important to define the ground truth for each slide separately, to test the hypotheses (H1.1 – H.1.4). For the slides that were not spiked, all FOVs that were captured through the AI-DP will be manually annotated by one trained laboratory technician. A second trained laboratory technician will then verify the annotations. In case of disagreement, a third trained laboratory technician will make the final call. For the spiked samples, the ground truth (samples being classified as MHI infection) is already established through the process of spiking.

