### 3 Processing KK thick smears with our AI-DP (KK2.0)

Processing KK thick smears with the AI-DP (KK2.0) is graphically illustrated in **Fig 1**. To facilitate study management, the AI-DP enables EDC for registering study participants (**step 1**) and provides QR printing spreadsheets and QR label templates. Once the KK thick smears are prepared (with QR code on the slide) (**step 2**), the scanning process is initiated (**step 3**). This involves manually loading of the smears into the scanner using a specialized slide holder, after which the QR code is read, and boundary of the stool smear is determined. If required, the user is prompted to manually adjust the scan boundary. In a next step, the slide is automatically scanned, and the scanner captures focus stacks, saving eight images at every field-of-view (FOV) within the KK thick smear (**step 3**). Following slide scanning, images are transferred to the Slide Manager, and FOVs are analyzed by the AI model for the detection, classification, and quantification of helminth eggs (**step 4**). In a final step, the results generated by the AI undergo review and verification (**step 5**). This is done through the EggInspector tool, presenting all the AI-determinants from a slide to a trained verifier.

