**Fig 4 pone.0309816.g004:**
[figure not shown]
Overview of the study design for the experiment on the repeatability and reproducibility. Figure created using BioRender.com.

**Fig 4** provides an overview of the proposed study design for the experiment on the repeatability and reproducibility. For this experiment, we will use a subset of the KK thick smears prepared during the experiment on the diagnostic performance. The subset will comprise two slide boxes, each containing 45 KK thick smears. To ensure we assess the repeatability and reproducibility across different egg counts, we will randomly select 30 negative KK thick smears, 30 smears with a total egg count for any helminths (*Ascaris*, *Trichuri*s and *S*. *mansoni*) between 1 and 100, and 30 smears with a total egg count greater than 100, resulting in a total of 90 smears. We will ensure that at least 50% of the KK thick smears in each box contain eggs from at least two different helminth species.

For the repeatability and reproducibility of the scanning process (KK2.0), all KK thick smears in slide box #1 (green) and box #2 (blue) will undergo two rounds of scanning. To ensure the entire sample is scanned, boundaries will be set larger than the smear for every scan, limiting interference and error caused by human error. The repeatability and reproducibility of the scanner process will be based on the final test results generated by the complete scanning process, which includes slide loading, boundary setting, device calibration, automatic focus setting, scan algorithms, AI detections and egg grouping algorithms. For the repeatability and reproducibility of the result verification process, the AI results of the unique scans of scanner #1 (red frame) will be verified by at least two different microscopists. For KK1.0, the examination of the KK thick smears will be conducted using the same flow as applied for the AI verification process. We will ensure that the same microscopists examine the same slides for both KK1.0 and do the AI verification for KK2.0.

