#### 4.4 Cost-efficiency

For this experiment, we built up on two general frameworks that were previously developed to support cost-efficient study design choices for large-scale STH deworming programs, including epidemiological surveys to reduce/stop large-scale deworming programs and to declare STH eliminated as a public health problem [40, 41], and to monitor the therapeutic drug efficacy [22]. Generally, these frameworks consist of three consecutive steps. In the **first step**, an in-depth analysis of the operational costs to process one stool sample is conducted for each diagnostic tool. In the **second step**, simulation studies are performed to determine the probability of making the reliable program decision. In the **third step**, the outcome of the cost assessment is integrated into the simulation study to estimate the total survey costs and determined the most cost-efficient study design. For the in-depth analysis of the operational costs to process one sample, we will both conduct an itemized cost assessment and determine the salary costs, which will be a function of the time-to-result (see **section 4.3**). For the simulation, we will deploy simulation frameworks previously published by both Kazienga et al. (2023) and Coffeng et al. (2023) [22, 40]. Both frameworks account for different sources of variation in egg counts, including (i) variability in mean egg intensity between schools; (ii) inter-individual variability in mean egg intensity due to variation in infection levels between individuals, where the level of aggregation is a linear function of the school-level mean egg intensity; (iii) day-to-day variability in mean egg intensity within an individual due to heterogeneous egg excretion over time; (iv) variability in egg counts between repeated aliquots of a stool sample due to the aggregated distribution of eggs in stool; (v) inter-individual variability in the effect of drug administration. Through the outputs of the experiment on both the diagnostic performance (**section 4.1**), and the repeatability and reproducibility (**section 4.2**), we will be able to further customize the simulation work to KK2.0 (e.g., additional variation in test results due to AI verification process and imperfect egg recovery).

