### Estimates of diagnostic performance are not absolute, but relative to KK1.0

For many infectious diseases, the absence of a gold standard (100% sensitivity and specificity) is a universal challenge to estimate the true performance of new diagnostics [47, 48]. To overcome this obstacle for STHs, it has been suggested to examine more stool samples with multiple diagnostic methods [49–52], and to deploy statistical methodologies that account for the absence of a gold standard [48]. In our study, we will determine the diagnostic performance of the AI-DP relative to the current diagnostic standard (KK1.0). In our opinion choosing KK1.0 as a sole comparator is justified. First, the AI-DP aims to improve the current KK1.0, and hence it is the obvious comparator to test the non-inferiority hypotheses. Second, for MHI infections, KK1.0 remains the sole diagnostic method to define the intensity of infections [23, 24]. Third, it has recently been shown that the clinical specificity, rather than the clinical sensitivity, will become more important when programs progress towards control and elimination of STH [23, 53]. Clinical specificity of KK1.0 thick smear (95% [16, 25, 26]) has never been considered as a drawback, which takes away the need for a more sensitive comparator (e.g., qPCR [15, 54]). Finally, we carefully designed the experiments so that we can ensure the true underlying infection status. For the KK smears representing no infections or infections of low intensity, we will have the ground truth based on the scans of the KK thick smears, while for the smears representing MHI infections we will spike the slides with known number of eggs. This design allows us to draw the appropriate conclusions around the defined non-inferiority hypotheses without the need of other diagnostic methods (e.g., qPCR) or more complex statistical models that account for a gold standard.

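### Ground truth for unspiked smears comes from KK2.0's own scan, so eggs lost at scanning bias H1.1, H1.3 and H1.4 towards non-inferiority by an unknown amount

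*Protocol article*

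**What the plan says.** All references are to the protocol article.

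- **Reference, unspiked smears (section 4.1, after Fig 3).** "For the slides that were not spiked, all FOVs that were captured through the AI-DP will be manually annotated by one trained laboratory technician". Then: "A second trained laboratory technician will then verify the annotations". A third technician settles disagreements. All three work on the same images.
- **Reference, spiked smears (same paragraph).** "For the spiked samples, the ground truth (samples being classified as MHI infection) is already established through the process of spiking".
- **What belongs to KK2.0 (section 3).** Scanning is step 3 of the index test: the smear boundary is determined, with manual adjustment when the user is prompted, and then "the slide is automatically scanned, and the scanner captures focus stacks, saving eight images at every field-of-view (FOV) within the KK thick smear".
- **Coverage of the smear (section 4.2).** For the repeatability experiment, "boundaries will be set larger than the smear for every scan", so that the whole sample is scanned. Section 4.1 has no such statement.
- **Decision rule (sections 5.1.1 and 6.1.1).** Both tests process the same smear. KK2.0 is non-inferior if the lower limit of the adjusted 90% interval for KK2.0 minus KK1.0 excludes -5 points. The significance level is 0.05/3.
- **Validity claim (Discussion, subsection on estimates being relative to KK1.0).** For smears with no or low-intensity infection, "we will have the ground truth based on the scans of the KK thick smears". The same paragraph says "we carefully designed the experiments so that we can ensure the true underlying infection status".
- **Use downstream (section 4.4).** Results of the diagnostic experiment customise the cost simulation, for example for "additional variation in test results due to AI verification process and imperfect egg recovery".

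**The concern.** The reference shares a step with one of the two tests it judges. An egg outside the scan boundary, out of focus in every image, or cleared before the scan is absent both from the KK2.0 result and from the truth. KK1.0 reads the physical smear and can still see it.

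If all eggs of a species are lost in this way, three things happen to that smear. It leaves the sensitivity denominator, so KK2.0 is not charged with a miss. It enters the specificity denominator as a true negative for KK2.0. If KK1.0 found the egg, it becomes a false positive for KK1.0. In a one-directional non-inferiority test these all help KK2.0, and neither more smears nor more annotators of the same images removes the effect.

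Three of the four primary diagnostic hypotheses (H1.1, H1.3, H1.4) use this reference. The detection limit (S1.2) and egg recovery (S1.3) use it too, and the cost hypotheses (H4.1, H4.2) draw on those results.

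**Working it through.** **1. Which errors the reference can see**

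- Egg captured in an image but missed by the AI or the verifier: the technicians annotate every captured field, so KK2.0 is charged.
- Egg lost at scanning, unspiked smear: not seen, KK2.0 is not charged.
- Egg lost at scanning, spiked smear: the truth is independent of the scan, so KK2.0 is charged. This largely protects H1.2.

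**2. Plan's own figure**

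Section 5.1.1 gives 225 negative smears per species for H1.3. Simulating the paired Newcombe interval at the 95% KK1.0 specificity quoted in the Discussion, with equal specificities, one-sided 0.05/3 and a 5-point margin, power at 225 is 56%, 69% and 81% for between-test correlations of 0, 0.3 and 0.5. The article gives no correlation. So 225 is attainable (at about 0.5) but neither confirmed nor contradicted, and the present point does not depend on it.

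**3. Size of the distortion, under assumptions**

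Let pi be the share of smears truly infected, m the share of those with no egg of the species in the captured images, and s the share of the wholly missed smears that KK1.0 calls positive. Both tests are taken as equally sensitive on captured smears.

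- Hidden sensitivity deficit of KK2.0 = m × s, while the table shows 0.
- Artificial specificity advantage of KK2.0 = pi × m × s / (1 − pi + pi × m).

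With s = 0.8 and pi = 0.30 (both assumed):

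| m | Hidden sensitivity deficit | Artificial specificity gain |
|---|---|---|
| 5% | 0.05 × 0.8 = 4 points | 0.012/0.715 = 1.7 points |
| 10% | 0.10 × 0.8 = 8 points | 0.024/0.730 = 3.3 points |
| 20% | 0.20 × 0.8 = 16 points | 0.048/0.760 = 6.3 points |

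With s = 0.5 the hidden deficits fall to 2.5, 5 and 10 points.

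Effect on the decision for H1.1 at the planned 125 *Ascaris* smears (assumed sensitivity 0.90 on captured and missed smears, correlation 0.3): with m = 10% the true difference is −9 points. The simulated chance of concluding non-inferiority is about 0.1% with an independent truth and about 24% with the scan-based truth.

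**4. How much loss is needed to change a label**

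- *Presence or absence (H1.1, H1.3).* Every egg of the species must be lost. If 5% of eggs were lost independently, a one-egg smear would be wholly missed 5% of the time and a two-egg smear 0.05² = 0.25% of the time; for five eggs it is negligible (0.05⁵). Very light infections, clustered loss or whole-scan failures therefore drive m.
- *Intensity class (H1.4).* Partial loss is enough. Section 4.1 puts the *Trichuris* spiking threshold above 42 eggs. An unspiked smear with 44 eggs that loses 3 is read as 41, is labelled low, and a correct moderate-to-heavy call by KK1.0 becomes a false positive.

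**5. Hookworm**

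The Introduction says hookworm eggs disappear if a smear is not examined within 1 h. Section 4.1 alternates KK1.0 and KK2.0 by participant ID, taken here as the order of reading. Where KK1.0 reads first, eggs can clear before the scan that defines the truth. Alternation does not cure this, because the truth comes from the scan in both orders.

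**6. Would a composite reference (scan annotation or KK1.0 positive) settle it?**

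Take perfect scanning and truly equal tests with 95% specificity. Under the composite, KK1.0 specificity is 100% by construction. KK2.0's false-positive rate among KK1.0-negative smears is (0.05 − P)/0.95, where P = 0.0025 + 0.0475 × correlation.

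| Correlation | Spurious KK2.0 deficit | P(non-inferior), scan truth, n = 225 | P(non-inferior), composite |
|---|---|---|---|
| 0 | 0.0475/0.95 = 5.0 points | 56% | 0.7% |
| 0.3 | 0.03325/0.95 = 3.5 points | 69% | 7% |
| 0.5 | 0.02375/0.95 = 2.5 points | 81% | 25% |

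Sensitivity is distorted as well. With 80% sensitivity and 30% prevalence, composite positives are 0.30 + 0.70 × 0.05 = 0.335. KK2.0 then looks worse by 0.03325/0.335 = 9.9 points at correlation 0 and by 0.016625/0.335 = 5.0 points at 0.5. The composite is a harsh bound, not a fair second test.

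**The case against.** The strongest reply is that no miss rate of 5% to 10% has any anchor in the article. Averaged over all low-intensity smears, such a rate would need failed scans, clustered loss or mostly one-egg smears. Wholly missed smears would also tend to hold few eggs, where KK1.0 is itself weak, so s = 0.8 is probably generous. The preliminary data in the Introduction show KK2.0 detecting more *Ascaris* (49.8% against 37.6%) and comparable *Trichuris* and hookworm. This stands as far as size goes: the figures above illustrate and do not estimate. It does not remove the mechanism or its direction.

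The article also says that no gold standard exists and that its estimates are relative to KK1.0. That helps little, since the bias lies in the relative comparison itself.

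Three stronger readings are tempting and not supported:

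- A reader might infer that KK2.0 is never charged for a scan miss. Spiked smears charge it.
- A reader might infer that the enlarged scan boundary is confined to the repeatability experiment. The article states it there and is silent elsewhere; a condensed article does not show that it is absent.
- A reader might infer that non-inferiority should have to hold under both the scan-based and the composite reference. At the protocol's 95% specificity that rule would usually reject truly equal tests.

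**Conclusion.** The point holds as a structural bias of known direction and unknown size. For unspiked smears the reference is an output of KK2.0, and no stated step lets the physical smear or a KK1.0 positive correct it. Scan losses therefore favour KK2.0 in H1.1, H1.3 and H1.4 and pass into S1.2, S1.3 and the cost simulation. H1.2 is largely protected where moderate-to-heavy smears are spiked.

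The article does not support inferring that the bias is large or that the non-inferiority conclusions must be wrong. The 4-point and 8-point hidden deficits rest on assumed whole-smear miss rates of 5% and 10% and on KK1.0 detecting 80% of those smears. What is wrong as written is the Discussion's statement that the design ensures true infection status: it ensures only the status visible in the scan.

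**What to change.** 1. From data already collected, tabulate by species and reading order every unspiked smear that is KK1.0-positive but negative on the scan annotation, and every smear that KK1.0 places in a higher intensity class than the scan-based truth.
2. Keep the scan annotation as the primary reference. Report the composite (scan annotation or KK1.0 positive) only as a worst-case bound, labelled as such, and not as a second condition for claiming non-inferiority.
3. Word the conclusions on H1.1, H1.3 and H1.4, and the egg recovery rate, as relative to eggs visible in the KK2.0 scan. Carry a range for scan loss into the cost simulation.
4. Replace the Discussion statement on true infection status with one that names this limit.

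Where feasible, a blinded re-look at the discordant smears would resolve many of them. Section 4.1 already stores smears at 4°C, although hookworm would need prompt re-reading. The fix does not depend on this step.

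The cost is a few extra tables and a more cautious claim. No change to recruitment or to the primary analysis is needed.

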#### 4.2 Repeatability and reproducibility

In this experiment, we will be evaluating the two parameters repeatability and reproducibility. Repeatability refers to the variability in test results (*Ascaris*, *Trichuris* and *S*. *mansoni*) when the same KK thick smear is examined by the same operator (e.g. scanner of AI-DP/microscopist), so called intra-annotator agreement, while reproducibility refers to the variability in test results when the same slide is examined by a different operator (e.g. scanner of AI-DP/microscopist), so called inter-annotator agreement (see also **Fig 4** for graphic definition of both repeatability and reproducibility). For KK2.0, we will focus on the scanning process (step 3 in **Fig 2**) and the AI verification process (step 5 in **Fig 2**). For KK1.0, we will focus on the egg counting process only (see also **Fig 4**). Generally, we hypothesise that both the repeatability and reproducibility of KK2.0 is at least 99%.

**Fig 4 pone.0309816.g004:**
[figure not shown]
Overview of the study design for the experiment on the repeatability and reproducibility. Figure created using BioRender.com.

**Fig 4** provides an overview of the proposed study design for the experiment on the repeatability and reproducibility. For this experiment, we will use a subset of the KK thick smears prepared during the experiment on the diagnostic performance. The subset will comprise two slide boxes, each containing 45 KK thick smears. To ensure we assess the repeatability and reproducibility across different egg counts, we will randomly select 30 negative KK thick smears, 30 smears with a total egg count for any helminths (*Ascaris*, *Trichuri*s and *S*. *mansoni*) between 1 and 100, and 30 smears with a total egg count greater than 100, resulting in a total of 90 smears. We will ensure that at least 50% of the KK thick smears in each box contain eggs from at least two different helminth species.

For the repeatability and reproducibility of the scanning process (KK2.0), all KK thick smears in slide box #1 (green) and box #2 (blue) will undergo two rounds of scanning. To ensure the entire sample is scanned, boundaries will be set larger than the smear for every scan, limiting interference and error caused by human error. The repeatability and reproducibility of the scanner process will be based on the final test results generated by the complete scanning process, which includes slide loading, boundary setting, device calibration, automatic focus setting, scan algorithms, AI detections and egg grouping algorithms. For the repeatability and reproducibility of the result verification process, the AI results of the unique scans of scanner #1 (red frame) will be verified by at least two different microscopists. For KK1.0, the examination of the KK thick smears will be conducted using the same flow as applied for the AI verification process. We will ensure that the same microscopists examine the same slides for both KK1.0 and do the AI verification for KK2.0.

#### 4.3 Time-to-result

During the experiments on the diagnostic performance (**section 4.1**), and repeatability and reproducibility (**section 4.2**), four different steps of the KK2.0 procedure will be timed. The four steps involve (i) participant registration (step 1 in **Fig 1**), (ii) the scanning process (step 3 in **Fig 1**), (iii) the AI process (step 4 in **Fig 1**), and (iv) the verification process (step 5 in **Fig 1**). The time required for each of these steps to be completed will be recorded by the AI-DP. The total time-to-result will be defined as the sum of the durations needed for the individual steps. Furthermore, in the Ugandan field setting, the time for setting up the AI-DP system at the different field locations will be recorded. The time-to-result for KK1.0 will not be measured in the present study. This has been intensively researched elsewhere as part of four clinical trials, each trial conducted in a different country [29, 34]. We will use these data as a comparator for KK2.0.

#### 4.4 Cost-efficiency

For this experiment, we built up on two general frameworks that were previously developed to support cost-efficient study design choices for large-scale STH deworming programs, including epidemiological surveys to reduce/stop large-scale deworming programs and to declare STH eliminated as a public health problem [40, 41], and to monitor the therapeutic drug efficacy [22]. Generally, these frameworks consist of three consecutive steps. In the **first step**, an in-depth analysis of the operational costs to process one stool sample is conducted for each diagnostic tool. In the **second step**, simulation studies are performed to determine the probability of making the reliable program decision. In the **third step**, the outcome of the cost assessment is integrated into the simulation study to estimate the total survey costs and determined the most cost-efficient study design. For the in-depth analysis of the operational costs to process one sample, we will both conduct an itemized cost assessment and determine the salary costs, which will be a function of the time-to-result (see **section 4.3**). For the simulation, we will deploy simulation frameworks previously published by both Kazienga et al. (2023) and Coffeng et al. (2023) [22, 40]. Both frameworks account for different sources of variation in egg counts, including (i) variability in mean egg intensity between schools; (ii) inter-individual variability in mean egg intensity due to variation in infection levels between individuals, where the level of aggregation is a linear function of the school-level mean egg intensity; (iii) day-to-day variability in mean egg intensity within an individual due to heterogeneous egg excretion over time; (iv) variability in egg counts between repeated aliquots of a stool sample due to the aggregated distribution of eggs in stool; (v) inter-individual variability in the effect of drug administration. Through the outputs of the experiment on both the diagnostic performance (**section 4.1**), and the repeatability and reproducibility (**section 4.2**), we will be able to further customize the simulation work to KK2.0 (e.g., additional variation in test results due to AI verification process and imperfect egg recovery).

